### Randomization and period allocation

Sites’ sequence randomization will be computer generated by a biostatistician from the clinical research platform URC-Est, independent of the study and before the study starts. Randomization will be stratified on country and center size.

### Data collection and data management

Data will be collected in an electronic case report form (e-CRF by the ED investigators with the help of clinical research technicians (CRT)). This e-CRF comprises baseline characteristics (past medical history, systolic blood pressure, heart rate, and other items from PERC, Wells and YEARS decision rules). Follow-up at 3 months will be done by phone interview of the patient or their general practitioner, outpatient consultation, email, or hospital visit. Outcome data recorded at follow-up will be entered in the same e-CRF as any serious adverse events that might occur.

### Statistical analysis plan

The complete statistical plan can be seen in the appendix (Supplementary file 2).

No interim analysis is planned. Analysis will be performed at the end of the study after data review and freezing of the data base. Baseline patient characteristics will be considered at the cluster (center) and patient levels. For the center level, characteristics at the beginning of the study will be described (there are no expected changes between the two periods for cluster characteristics). Baseline characteristics of patients will be described globally and according to the group of intervention. Continuous variables will be summarized using descriptive statistics, i.e., number of subjects, mean, median, standard deviation (SD), inter quartile range, minimum and maximum. Categorical variables will be summarized by frequency and percentage.

Since this is a non-inferiority study, analysis of the principal criterion will be performed on the per-protocol population (patients without major protocol deviation as no respect of selection criteria, no respect of strategy assigned by randomization, missing values for the principal criteria, or other major protocol deviation identified during data review before freezing of the data base). A sensitivity analysis will be performed on the intention-to-treat population (all randomized patients, except those that withdrew consent). Given the rare occurrence of a thrombo-embolic (TE) event, a generalized linear regression mixed model with Poisson distribution (log link) will be performed (Poisson model for proportions), taking into account a random effect for each center and considering period and strategy-by-period interactions as fixed effects. The decision rule will be based on the upper bound of the 95% two-sided CI of the incidence rates ratio of TE events. Any missing value will be considered as a failure. Secondly, sensitivity analysis will be performed using the 95% two-sided CI of the difference of percentage of TE events between groups. If the upper bound of the CI is above 1.35% of the difference, the inferiority hypothesis of the intervention group will be rejected. Secondary criteria will be compared between groups on the intention-to-treat population and under the superiority hypothesis. The proportions of irradiative imaging, of introduction of anticoagulation regimen, of hospital admission following the ED visit, of all causes of hospital readmission at 3 months, and of all-cause death at 3 months will be compared between groups by using generalized linear regression mixed models with Poisson distribution (log link), taking into account a random effect for each center and considering period and strategy-by-period interaction as fixed effects. If the number of events is sufficient, generalized linear regression mixed modeling with Bernoulli distribution (logit link) will be performed. The proportion difference between groups and its 95% CI will be calculated.

The ED length of stay will be compared between the two periods using a linear regression mixed model, taking into account a random effect for each center and considering period and strategy-by-period interaction as fixed effects. In case of non-normality distribution of the interest variable, a transformation could be performed or a model appropriate to data distribution could be selected.

Differences between groups in the proportion of patients with diagnosed PE at 3-month follow-up, excluding isolated sub-segmental PE, among patients in whom PE has been initially ruled out, will be calculated as well its 95% CI. If possible, generalized linear regression mixed models with Poisson distribution (log link) will be performed. A random effect for each cluster will be considered and considered fixed effects will be period and strategy-by-period interactions. If the number of events is sufficient, generalized linear regression mixed modeling with Bernoulli distribution (logit link) could be performed. The proportion of patients with a diagnosed TE event at 3-month follow-up (either a PE or a deep venous thrombosis), among patients in whom PE was initially ruled out by the PEPS score, will be described with its 95% CI.

Sensitivity analysis will be performed on the per-protocol population. Missing values for secondary criteria will not be replaced. All superiority tests will be two-sided and *p* values less than 0.05 will be considered significant.

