### Sample size calculation

In the recent recommendations of the International Society of Thrombosis and Hemostasis on studies for PE diagnosis in the ED, it has been suggested that the maximum acceptable failure rate of a tested strategy should not exceed 1.85% [3]. The recent large European prospective cohort studies on PE diagnosis (PROPER, PERCEPIC, YEARS, ADJUST-PE) reported a failure rate of 0.1–0.5%. With an anticipated failure rate of 0.5% in the control group, a non-inferiority margin set at 1.35% (according to the ISTH recommendations so the upper bound of the 95% confidence interval (CI) of the failure rate in the intervention group will not exceed 1.85%), beta = 20%, and one-sided alpha = 2.5%, N1 = 857 patients are needed (East 6, Cytel, Cambridge, MA, USA). Under the assumption of an intra-class correlation coefficient (CCIC) of 0.018, an interperiod correlation (η) of 0.0115 (based on previous cluster randomized trials in French EDs) and a mean cluster size for one period (m) = 22 patients, the cluster design effect would be 1.37 [17, 20]. Considering 5% of non-evaluable patients, with 18 centers and two periods, 1234 patients are needed.

Besides the non-inferiority analysis, it is of utmost importance that the upper bound of the 95% CI of the failure rate of the tested modified diagnostic strategy remains below 1.85%, whatever the rate of the control group is. Our retrospective study reported an anticipated failure rate at 0.85% but focused only on low risk patients. Therefore, with an anticipated failure rate of 1% in the intervention period, the sample size of this group should be at least 700 to respect the maximal upper bound of 1.85%.

Therefore, for a conservative approach to these two conditions (non-inferiority margin at 1.35% and maximal upper bound of the 95% CI below 1.85%), 1400 (700 in each group) subjects will be needed in this study.

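### The primary Poisson model carries a strategy-by-period interaction that about 7 expected events cannot support, while the decision rests on a single rate ratio

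*Protocol article*

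**What the plan says.** In the Protocol article, under Statistical analysis plan, the primary endpoint is analysed on the per-protocol population, and the type of model is given as "a generalized linear regression mixed model with Poisson distribution (log link) will be performed (Poisson model for proportions". The centre effect and the fixed effects of that model are specified in these words: "taking into account a random effect for each center and considering period and strategy-by-period interactions as fixed effects". The strategy main effect is not listed separately. The decision then depends on one number: "The decision rule will be based on the upper bound of the 95% two-sided CI of the incidence rates ratio of TE events".

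The text does not describe the interaction as a term to be tested and dropped, and does not say that the ratio is averaged over the two periods. For the primary endpoint it names no alternative if the model cannot be estimated. A confidence interval for the difference in percentages is planned, but as a sensitivity analysis. Choosing the model by the number of events is mentioned only for secondary endpoints.

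The same fixed effects recur for the secondary proportions, for length of stay, and for PE excluding isolated sub-segmental PE ("A random effect for each cluster will be considered and considered fixed effects will be period and strategy-by-period interactions"), so the term is deliberate.

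The figures that determine the number of events are under Sample size calculation: "With an anticipated failure rate of 0.5% in the control group, a non-inferiority margin set at 1.35" percentage points, and a final size of 1400, 700 per group. Study design splits this over two periods, with 350 patients per strategy in each.

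**The concern.** With strategy, period and their interaction in the model, the fixed effects are saturated: each of the four strategy-by-period cells has its own rate, estimated from that cell's events alone. Two consequences follow.

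- **Estimability.** A cell with no events sends its log rate to minus infinity. A random centre effect does not prevent this. Any ratio that uses that cell then has no finite estimate or Wald interval.
- **Meaning of the ratio.** An interaction model contains two strategy ratios, one per period. A single ratio has to be either one of them or an average. Within one period each centre applies only one strategy, so a one-period ratio compares centres with centres and leaves out the within-centre comparison that the cross-over provides. In a two-sequence, two-period design the interaction is also aliased with sequence and carry-over, which the 1-month wash-out already addresses by design.

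At stake is whether the primary confidence interval exists when the database is frozen, and which comparison it describes.

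**Working it through.** **1. The plan's own figure.** Inputs: "beta = 20%, and one-sided alpha = 2.5%, N1 = 857 patients are needed", 0.5% in both groups, margin 1.35 percentage points. Per arm: (1.960 + 0.842)² × 2 × 0.005 × 0.995 / 0.0135² = 428.5, so 857 in total, as stated. Then 857 × 1.37 = 1174; dividing by 0.95 gives 1236 and multiplying by 1.05 gives 1233, close to the stated 1234. The planning rate and margin are therefore read correctly. The final size of 1400 comes from the second condition: "with an anticipated failure rate of 1% in the intervention period, the sample size of this group should be at least 700".

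**2. Expected events.**
- 1400 × 0.005 = 7.0 in total; 350 × 0.005 = 1.75 per cell.
- With 1% in the intervention: 350 × 0.01 = 3.5 per intervention cell, 10.5 events in total.

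**3. Chance of an empty cell** (independent Poisson counts). P(cell empty) is exp(−1.75) = 0.174 at 0.5% and exp(−3.5) = 0.030 at 1%.

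| Ratio reported | Fails if | 0.5% / 0.5% | 0.5% / 1% |
|---|---|---|---|
| Interaction model, averaged over periods | any of four cells is empty | 1 − 0.826⁴ = 53% | 1 − 0.826² × 0.970² = 36% |
| Interaction model, one reference period | either of two cells is empty | 1 − 0.826² = 32% | 1 − 0.826 × 0.970 = 20% |
| Strategy and period only | a whole arm has no events | 1 − (1 − exp(−3.5))² = 5.9% | 1 − 0.970 × (1 − exp(−7)) = 3% |

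**4. Sensitivity of these figures.**
- *Clustering.* A simulation used the protocol's intra-class correlation of 0.018 and interperiod correlation of 0.0115, with gamma frailties and 20 centres × 35 or 18 centres × 39 patients per period. The chance of an empty cell rises from 53% to 66%, and from 36% to 47–49%. The chance of an arm without events at 0.5% rises to about 12%.
- *5% loss.* 350 × 0.95 × 0.005 = 1.66 per cell; P(any cell empty) = 57%.
- *Lower rate.* The earlier cohorts "reported a failure rate of 0.1–0.5" per cent. At 0.1% there are 0.35 events per cell and P(any cell empty) = 99%.
- *Denominator.* The endpoint counts only patients in whom PE was initially ruled out, and the primary population is per-protocol, so cells will hold fewer than 350. The figures in the table favour the plan.

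**5. Precision when the ratio can be estimated** (0.5% in both strategies, expected counts, clustering ignored).
- One period: SE of the log ratio = √(2/1.75) = 1.07; upper bound exp(1.96 × 1.069) = 8.1 times the estimate.
- Strategy and period only: √(2/3.5) = 0.756; upper bound 4.4 times the estimate.
- Interaction model averaged over periods: ½√(4/1.75) = 0.756, the same as without the interaction.

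**6. One data set, three answers.** Take control counts of 2 and 1 in periods 1 and 2, and intervention counts of 1 and 3.
- Without the interaction: 1.33 (0.30 to 5.96).
- With it, period 1 as reference: 0.50 (0.05 to 5.51).
- With it, averaged over periods: 1.22 (0.24 to 6.37).

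**The case against.** Five arguments can be made for the plan.

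- **The article names terms, not a coding.** This stands. A reader might infer that the interaction by itself turns the primary ratio into a one-period effect and nearly doubles the upper bound (8.1 against 4.4 times the estimate). The documents do not support that: it holds only for a reference-coded coefficient, and step 5 shows that averaging restores the SE of 0.756. Averaging does not help with empty cells, however, because it needs all four.
- **Secondary outcomes are not harmed in the same way.** This also stands. A reader might infer that the term removes cross-over precision for imaging, admission and length of stay. In a balanced design the interaction is a between-centre term, orthogonal to the within-centre strategy effect. In an illustrative balanced linear mixed model (20 centres, 35 patients per period) the SE was 0.0537 both without the interaction and with it centred; only the uncentred one-period coefficient lost precision (0.244). Common outcomes do not have empty cells either.
- **The full statistical plan is a supplementary file and may settle contrast and convergence.** It may, and their absence from the article is not the point. The point is that the article itself fixes an interaction in a model with about 7 events.
- **Other safety results remain.** The interval for the difference in percentages, and the requirement that the intervention arm's upper bound stay below 1.85%, need no cell-specific log rates. An empty cell therefore does not leave the trial without a safety result. But the decision rule is tied to the ratio, and the difference is labelled a sensitivity analysis.
- **Missing outcomes counted as failures would fill the cells.** With 5% missing, that rule would add about 1400 × 0.05 = 70 events. But the same section excludes patients with a missing primary outcome from the per-protocol set on which the primary analysis is run, so about 7 events remains the applicable count.

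**Conclusion.** The concern holds for the primary analysis. As written, the model has about an even chance (53%; 36% at 0.5%/1%) of giving no finite ratio averaged over periods, or about a one-in-three chance (32% at 0.5%/0.5%) if one reference period is used. Clustering at the protocol's own correlations raises the first two figures to 66% and 47–49%. If the one-period coefficient is used and can be estimated, it is a between-centre contrast with SE of about 1.07 against 0.76; this part depends on the coding.

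These results assume 350 patients per cell, failure rates as planned, true events only, and an ordinary unpenalised likelihood fit. For common secondary outcomes and length of stay the remaining issue is small: the article does not say that the strategy effect is taken over both periods.

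**What to change.** - **Primary model:** strategy and period as the only fixed effects, with the centre random effect. State that the decision ratio is the strategy effect over both periods.
- **Strategy-by-period results:** a descriptive sensitivity table of events and denominators by strategy and period, with no role in the decision.
- **Small-event rule:** dropping the interaction reduces the estimation problem but does not remove it. An arm without events remains possible in about 6% of trials at 0.5% (about 12% with clustering) and about 75% at 0.1% (1 − (1 − exp(−0.7))²). Pre-specify the method for that case, for example an exact or penalised-likelihood interval.
- **Secondary models:** drop the interaction in the same way, or state that the strategy effect is averaged over periods. For PE excluding sub-segmental PE, whose events are a subset of the primary ones, drop it.

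The cost is a change of wording before the database is frozen, with no effect on sample size or conduct. The downside is that carry-over is examined descriptively and not adjusted for, so the analysis relies on the wash-out.

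### The primary non-inferiority decision rests on a rate ratio with no stated limit, while the margin and sample size are for an absolute difference

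*Protocol article*

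**What the plan says.** **Margin and size (Protocol article, Sample size calculation).** The calculation begins "With an anticipated failure rate of 0.5% in the control group" and uses "a non-inferiority margin set at 1.35"%. The margin is chosen so that "the upper bound of the 95% confidence interval (CI) of the failure rate in the intervention group will not exceed 1.85"%, that is 0.5% + 1.35% = 1.85%. With one-sided alpha 2.5% and beta 20% this gives 857 patients. The total rises to 1234 with a design effect of 1.37 and 5% non-evaluable, and finally to 1400 (700 per group). The last step serves a separate condition: the upper confidence bound of the failure rate under the modified strategy (MODS) must stay below 1.85% whatever the control rate.

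**Primary analysis (Protocol article, Statistical analysis plan).** The model is "a generalized linear regression mixed model with Poisson distribution (log link) will be performed (Poisson model for proportions"), which estimates a ratio. The rule is "The decision rule will be based on the upper bound of the 95% two-sided CI of the incidence rates ratio of TE events". No value for that bound follows.

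**Where 1.35% is used (same section).** "Secondly, sensitivity analysis will be performed using the 95% two-sided CI of the difference of percentage of TE events between groups". The limit is attached to this analysis: "If the upper bound of the CI is above 1.35% of the difference, the inferiority hypothesis of the intervention group will be rejected".

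The Medico-economic evaluation section refers again to the upper bound of the rate-ratio interval, also without a value.

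**The concern.** A margin of 1.35 percentage points cannot be compared with the upper bound of a ratio. As written, the analysis that decides the trial has no limit to be judged against, and the analysis that has the limit does not decide. If the two disagree, the text gives the decision to the ratio.

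The scale matters here because the events are so rare. At 0.5% and 700 per arm about 3.5 failures per arm are expected. With counts that small, an absolute difference can be tightly bounded while a ratio cannot. The safety conclusion could then depend on the scale and on a ratio limit settled late, which a non-inferiority claim should not allow.

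**Working it through.** **Inputs from the article:** control failure rate 0.5%; margin 1.35 points; one-sided alpha 2.5% (z = 1.96); power 80% (z = 0.8416); 700 per arm; 5% non-evaluable; design effect 1.37. **Assumptions:** equal true rates of 0.5% (this is what reproduces 857), and a ratio limit of 1.85/0.5 = 3.7, the only one that the article's figures imply.

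**1. Reproduce the stated size on the difference scale.**
Total N = 2 × (1.96 + 0.8416)² × 2 × 0.005 × 0.995 / 0.0135² = 857.02, matching 857. The stated 80% power is therefore power for a risk difference.

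**2. The same requirement on the ratio scale.**
n per arm = 2 × (1.96 + 0.8416)² / [0.005 × (ln 3.7)²] ≈ 1835, or 3670 in total (about 18 events) before clustering and loss. With 1.37 and 5% loss it is about 5290.

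**3. Power of the ratio rule at 700 per arm, no clustering or loss.**
- Expected events per arm: 700 × 0.005 = 3.5.
- SE(log ratio) = √(1/3.5 + 1/3.5) = 0.756.
- Upper bound when the observed ratio is 1: exp(1.96 × 0.756) = 4.4, already above 3.7.
- Power = Φ(1.308/0.756 − 1.96) = Φ(−0.23) = 41%. Binomial enumeration of the Wald log-ratio interval, with zero-event arms counted as not concluding, gives 36%.
- Other ways of forming the interval, by enumeration: 27% (exact conditional), 47% (0.5 added to each cell).

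**4. Power of the ratio rule after loss and clustering.**
Effective n = 700 × 0.95 / 1.37 ≈ 485 per arm, or about 2.43 events. SE = √(2/2.43) ≈ 0.908. Power = Φ(1.308/0.908 − 1.96) ≈ 30%; by enumeration 22%.

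**5. Dependence on the assumed limit.**
The ratio limit needed for 80% power at 700 per arm is exp(2.8016 × 0.756) = 8.3. After loss and design effect it is about 12.7.

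**6. The difference rule on the same basis.**
Normal formula at 700 per arm: SE = √(2 × 0.005 × 0.995/700) = 0.00377, so power = Φ(0.0135/0.00377 − 1.96) = 95%. Enumerated:

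| Rule | 700 per arm | about 485 per arm |
|---|---|---|
| Difference, Wald | 92% | 84% |
| Difference, Newcombe | 85% | 65% |
| Ratio limit 3.7, Wald | 36% | 22% |

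**7. Arms without events.**
P(no event in a given arm) = 0.995^700 = 3.0%. P(at least one such arm) = 1 − (1 − 0.030)² = 5.9%. In those trials a Wald ratio interval cannot be computed.

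**The case against.** **The full statistical plan may state a ratio limit.** The article points to a supplementary plan that is not shown. A reader might infer that the primary test is known to be badly underpowered. The article does not support that as a fact: with no ratio limit stated, power on that scale is undetermined, and every ratio-scale power above is conditional. What stands is that the article's own decision rule and its own margin and sizing are on different scales. A limit given elsewhere would restore 80% only if it were above about 8.3.

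**The matching analysis is already planned.** True. The difference is specified and tied to 1.35%, so the defect is one of hierarchy, not omission.

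**A fixed ratio would let in an unsafe strategy.** A reader might infer that a limit of 3.7 would accept a MODS failure rate of 3.7% if the control rate were 1%. The separate 1.85% ceiling largely blocks this. A 1.35-point difference has a milder form of the same weakness (1% + 1.35% = 2.35%), so the ceiling is needed either way.

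**The advantage of the difference is partly a Wald result.** This also stands. With Newcombe intervals power is 85%, and about 65% after loss and design effect. The gap over the ratio rule remains large, but 80% is not assured.

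**The ratio interval fails in 6% of trials.** This holds for Wald intervals only. If only the MODS arm has no events, an exact conditional or profile-likelihood upper bound is finite; only a control arm with none leaves it unbounded.

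**Missing values counted as failures would raise the event count.** The same section says so. Under an assumed 2% missing per arm, the rate becomes 0.005 + 0.995 × 0.02 = 2.49%, about 17 counted failures per arm. Normal-approximation power is then about 97% for a ratio of 3.7 and 37% for the difference. The per-protocol definition removes patients with missing primary outcomes, so the rule may apply only to the intention-to-treat analysis. The figures above are for observed events.

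**Conclusion.** The inconsistency is in the text and does not depend on any assumption: margin, sample size and power are on the absolute scale, the primary decision is on the ratio scale without a limit, and the 1.35-point limit sits in a sensitivity analysis. The 80% power is not the power of the primary test.

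The size of the shortfall is conditional on equal true rates of 0.5%, observed events only, and an assumed limit of 3.7. Its direction is robust at that event rate, because any ratio limit below about 8.3 misses 80% under the most favourable conditions, with no clustering or loss. This should be corrected before the database is frozen, since a safety conclusion rests on it.

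**What to change.** - Make the absolute risk difference the primary decision rule: non-inferiority is concluded if the upper bound of the two-sided 95% CI is below 1.35 percentage points, with centre and period accounted for. The sentence that now carries the 1.35% limit is worded in the opposite direction and must be turned round when it becomes the primary rule.
- Name the interval method in advance, suited to very few events, and restate the power for it, including loss and clustering.
- Keep the separate 1.85% ceiling for the MODS arm.
- Report the incidence rate ratio from the Poisson mixed model as supportive, with no decision role.

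**Cost.** Wording in the protocol and statistical plan; no new data, since both analyses are already planned. The ratio becomes descriptive, and the restated power may be less favourable than 80% if a score-type interval is chosen.

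### The missing-equals-failure rule names no analysis population, conflicts with the per-protocol definition, and lets follow-up losses swamp a 0.5–1% event wherever it is applied

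*Protocol article*

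**What the plan says.** All the analysis rules stand in one paragraph of the Statistical analysis plan section of the protocol article.

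- Primary population: "analysis of the principal criterion will be performed on the per-protocol population". Among the major deviations that remove a patient from it are "missing values for the principal criteria".
- Supporting population: "A sensitivity analysis will be performed on the intention-to-treat population (all randomized patients, except those that withdrew consent").
- Primary decision: "The decision rule will be based on the upper bound of the 95% two-sided CI of the incidence rates ratio of TE events". No margin for that ratio is given.
- Directly after the decision rule: "Any missing value will be considered as a failure". No population and no strategy group is named.
- Then a second scale: "sensitivity analysis will be performed using the 95% two-sided CI of the difference of percentage of TE events between groups", with the 1.35-point margin.

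The Sample size calculation section expects 0.5% failures in the control group, allows 1% in the intervention group, and treats an upper 95% bound below 1.85% in the intervention group as essential. It plans for losses with "Considering 5% of non-evaluable patients" but gives no expected rate of missing primary outcomes.

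**The concern.** A patient with no three-month outcome cannot be left out of the primary analysis for that reason and also be counted in it as a failure. Two statisticians working from this paragraph could produce different primary results. Because the sentence follows the primary decision rule directly, reading it as part of the primary analysis is not far-fetched.

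The choice matters because the event is so rare. In 700 patients, 0.5% is 3.5 failures and 1% is 7. Losing 1% of patients to follow-up adds another 7 under this rule.

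The rule looks conservative but need not be. Adding the same number of imputed failures to both groups pulls a rate ratio towards 1, which favours non-inferiority on the scale used for the primary decision. On the difference scale it mainly adds variance and costs power.

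**Working it through.** **Inputs from the article (Sample size calculation):** control rate 0.5%; margin 1.35 points; one-sided alpha 2.5%; power 80%; design effect 1.37; 5% non-evaluable; 700 per group; intervention rate 1% for the 1.85% ceiling.

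**Assumptions, not in the article:** a proportion m of outcomes is missing, equal in both groups unless stated, with m from 0.5% to 5%; a ratio margin of 1.85/0.5 = 3.7; all 700 per group in the denominator (the endpoint counts only patients in whom embolism was initially ruled out, so the real denominators are somewhat smaller). The ratio and ceiling results ignore clustering.

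**The plan's own figures.** Per group, (1.96 + 0.8416)² × 2 × 0.005 × 0.995 / 0.0135² = 428.5, so 857 in total, as stated. 857 × 1.37 = 1174. Allowing 5% gives 1174/0.95 = 1236 or 1174 × 1.05 = 1233; the article has 1234. For the ceiling, 1% in 700 gives a Wald bound of 1% + 1.96 × √(0.01 × 0.99/700) = 1.74%, below 1.85%. Eight failures give 1.93%, so at most 7 failures pass.

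**Effect of the rule.** If missing counts as failure, a true rate p is observed as q = m + (1 − m)p.

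*Ratio.* True rates of 1.85% and 0.5% have a ratio of 3.70, exactly at the assumed margin. With 5% missing, q is 6.76% and 5.475%, and the ratio is 1.23. The false non-inferiority column is the simulated chance that the upper 95% bound of the ratio falls below 3.7.

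*Difference.* True rate 0.5% in both groups. SE = √(1.37 × 2q(1 − q)/700) and power = Φ(1.35/SE − 1.96), with SE in percentage points. With none missing, SE = 0.441 and power is 86%. With 5% missing, SE = 1.423 and power is 16%.

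*Ceiling.* The chance of at most 7 failures in 700, if the ceiling were judged on data imputed in this way.

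| Missing per group | Imputed failures in 700 | Observed ratio (true 3.70) | False non-inferiority, margin 3.7 | Power on difference, design effect 1.37 | Ceiling met, true 0.5% | Ceiling met, true 1% |
|---|---|---|---|---|---|---|
| 0 | 0 | 3.70 | about 3% | 86% | 97% | 60% |
| 0.5% | 3.5 | 2.35 | 18–19% | 58% | 60% | 18% |
| 1% | 7 | 1.89 | 41–43% | 43% | 18% | 3% |
| 2% | 14 | 1.53 | 79% | 28% | 0.4% | 0.04% |
| 5% | 35 | 1.23 | over 99% | 16% | about 0 | about 0 |

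Where a range is shown, repeat calculations differed by a point or two.

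**Unequal loss.** With 1% missing in control and 3% under MODS, the observed rates are 1.495% and 4.79%, the ratio is 3.21 and false non-inferiority is about 7%. With 1% and 5%, the ratio is 4.52 and false non-inferiority is about 0.5%, which is conservative.

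**If missing outcomes are excluded.** A 5% loss leaves 665 per group. At 1% the Wald bound is 1.76%, still below 1.85%. Under equal loss unrelated to outcome, the ratio keeps its true value.

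**The case against.** The strongest reply is that the two rules can coexist. The paragraph defines two populations. If missing outcomes leave the per-protocol set and count as failures only in the intention-to-treat set, nothing is contradictory and the primary analysis is untouched. That is a fair reading and may be the intended one, but the sentence does not say so, and its position after the primary decision rule points the other way.

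The inputs can also be challenged. The 5% is for non-evaluable patients, which can include selection errors or departures from the assigned strategy, so it is not a forecast of missing outcomes. The article excludes patients who are not expected to be reachable at three months and allows several routes of follow-up, so actual loss may be well under 5%. The ratio margin of 3.7 is inferred. Equal loss is assumed, and the direction is not guaranteed without it. The difference-scale test is itself labelled a sensitivity analysis. All of this stands, and it is why the sizes are given as a range under stated assumptions.

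A reader might go further and infer that the 1.85% ceiling becomes unreachable. The article does not say that the ceiling is judged on imputed data, and even if it were, it would be met 60% of the time with 0.5% missing at a true rate of 0.5%.

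**Conclusion.** The point holds as a conflict in the wording with a material consequence wherever the rule is used. In the primary per-protocol analysis the rule is either empty or overrides the definition of the set. In the intention-to-treat analysis, where it most naturally applies, the result can reflect follow-up losses more than missed embolism, so that analysis cannot serve as a check on the primary one.

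The size depends on how much is missing and how evenly. With equal loss, even 0.5% to 1% missing raises false non-inferiority on the ratio scale from about 3% to roughly 18–43% under the assumed margin, and 2% missing cuts power on the difference scale from about 86% to 28%. Excess loss under MODS weakens or reverses the ratio effect.

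The article does not support the stronger statement that the plan hides true inferiority. That would require the rule to apply to the primary analysis, similar losses in both groups, and a ratio margin that is not stated.

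**What to change.** Replace the sentence with one rule per population.

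1. Per-protocol (primary): patients with a missing primary outcome are excluded, as the definition already says, and the 1.85% ceiling is judged on this set.
2. Intention-to-treat (sensitivity): analyse observed outcomes rather than imputing failure in both groups. Add a tipping-point analysis that raises the failure probability among missing MODS patients relative to missing control patients. Its worst case counts missing MODS patients as failures and missing control patients as non-failures. Report the point at which the conclusion changes; the worst case marks the end of the range and is not a test to be passed.

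Multiple imputation by centre is not advisable. At the anticipated 0.5%, about 3–4 events per group spread over 18 to 20 centres and two periods cannot support it.

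The cost is a wording change in the protocol and analysis plan and a small amount of extra programming. Sample size and data collection are unaffected.
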